Starting in the week after baseline assessment, participants allocated to the RTG training will receive 14 visits, each lasting 1 hour, from a research therapist over a period of 6 weeks. This will replace any usual care training for the upper limb. The frequency of the research therapist’s visits will be three times a week for the first 3 weeks, twice a week for each of the next 2 weeks, then once in the final week. The frequency of visits is tapered with the aim of increasing self-efficacy in practice. The intensity of practice within each 1-hour session will be dependent on individual participant’s capabilities, but high numbers of repetitions will be encouraged, with the aim of delivering between 100 and 300 repetitions within each 1-hour session, in accordance with the findings of a recent feasibility study into frequency of task-specific training [52]. To facilitate such a high number of repetitions, clinical experience has indicated that it is appropriate to limit the number of exercises prescribed within each session to a maximum of six, and to a maximum of four for participants to continue to practice independently. The research therapist will keep a log of which exercises from the treatment manual are performed, and of the number of repetitions of each exercise.

From the beginning of the intervention phase, the participants will be instructed to practice in the absence of the therapist for 1 hour/day. They will be asked to record on a log sheet the number of repetitions of each task that they complete in their independent practice. There is no method in place in this feasibility study to check on the fidelity of these records, as this would have required resources beyond those available for this study. The therapist will stress to the participant that an accurate record is important to enable us to determine the feasibility of the amount of practice prescribed. They will be requested to record reasons for non-adherence to the practice schedule. This information will be collected at the end of the intervention period.

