### Control group

The control group will receive arm therapy in accordance with usual care, which will be delivered by NHS service therapists. In usual care, the frequency and content of physiotherapy or occupational therapy for improving upper-limb function is variable. From consultation with local therapy services, we found that provision of therapy varies in intensity, depending on the individual’s care pathway and the range of community services available. For example, after discharge from early supported discharge services, patients with care needs are usually referred to community intermediate care or rehabilitation teams. These teams typically provide a service for 6 weeks, and patients may receive approximately two visits per week from a qualified therapist, with 30 minutes of the visit focused on the arm or hand. There may be supplementary visits from support workers. Other patients may be seen by a community therapist once a fortnight with no supplementary visits from support staff, and some patients may not receive any therapy at all. It is unusual to receive arm therapy beyond 6 months after discharge from hospital. One of the aims of this feasibility study is to determine the frequency and content of treatment delivered in both arms of the trial. Usual care will be captured on recording sheets that will be completed by NHS service physiotherapists and occupational therapists. They will be asked to record the content, duration, and frequency of upper-limb treatment, including the number of repetitions of any functional task training on treatment recording sheets developed by Donaldson *et al*. [54].

Participants allocated to the control group will be provided with a booklet about recovery after stroke, which is the same as the booklet which will be given to the intervention group, with the exception that, instead of information about the RTG training, it will provide details of the frequency of assessment visits for the study (see Additional file 4).

Participants in the control group who do not receive any therapy aimed at improving upper-limb function during their participation will receive a single visit from the research physiotherapist after their final assessment. The physiotherapist will discuss the patient’s functional limitations and goals with them and, after assessing their movement and function, will provide specific exercises and advice. If indicated, the physiotherapist is able to refer to appropriate local therapy services.

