### Adverse events

Pain in the shoulder, upper arm and hand and oedema in the hand are common sequelae of hemiparesis, and are therefore expected AEs in the study. In addition, falls and equipment failure leading to injury requiring a visit to hospital or general practitioner will be treated as expected AEs. It is possible that increased use of the upper limb may lead to an increase in general activity in the home or community, and could result in increased likelihood of falling. The ARAT and WMFT assessments require that equipment is taken into the participant’s home. Although every effort will be made to minimize risk, accidents may happen when using any equipment. Participants will be specifically asked at each of the assessment visits if they have experienced any of the expected AEs.

All staff involved in contact with participants will receive training on identification and reporting of AEs. Any serious AEs that occur will be reported to the trial sponsor, and if the chief investigator (CI) considers any of these to be related to the RTG intervention, these AEs will be reported immediately to the research ethics committee that granted approval for the trial. Incidence of AEs will be collected by the trial manager and reported quarterly to the trial steering group.

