### Data analysis

As this is a feasibility study to test the levels of recruitment and retention of participants, and completeness of data that can be expected within a definitive multicenter trial, there will be no formal statistical testing, and results will instead be summarized using descriptive statistics.

Analysis of the centrally held screening log data will lead to a description of the characteristics of the recruited sample against the target population, and the percentage of refusals at the recruitment stage. Recruitment rates per month for each site will be determined. The number of withdrawals and reasons for withdrawal from the study will be assessed.

Compliance with the RTG intervention will be assessed by the number and duration of physiotherapy visits and the proportion of participants completing the 6-week intervention. The frequency of use of the exercises, number of repetitions, and duration of practice of each exercise, both within the physiotherapy sessions, and the independent practice will be summarized and compared with the intended exercise frequency and content. The frequency and content of the treatment received by each group will be summarized, as will the incidence of expected AEs and serious AEs. Responses to the participant questionnaire about the RTG training will be synthesized and examined to determine if any changes should be made to the intervention.

Completeness of outcome data will be determined, and data for each of the endpoints will be summarized; the mean differences between the arms, with their confidence intervals, will be presented. Assessment of the sample scores on the outcome measures, combined with a summary of participant preference for ARAT and WMFT, will be carried out to determine which arm function test should be used as the primary outcome measure for a phase III trial. Sample sizes for a subsequent phase III trial will be calculated, based on observed changes from baseline in performance, for both the control and intervention groups.

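### Adverse events reach the trial by two routes, one of which gives the RTG arm more reporting opportunity, and the planned summary neither separates the routes nor covers all AEs

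*Protocol article*

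**What the plan says.** Aim 8 (Study objectives) is the frequency of AEs in both groups, with no restriction by type.

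The Adverse events section sets two routes. Participants are asked directly about the expected AEs at each assessment visit. These AEs are arm and hand pain, hand oedema, and falls and equipment failure, with an injury and medical-visit condition. In addition, "All staff involved in contact with participants will receive training on identification and reporting of AEs".

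Under Outcome measurement, assessments follow the same schedule in both arms (baseline, then 7 weeks, 3 months and 6 months after randomization) and are done by a blinded assessor. Under Blinding, treating therapists and participants are not masked.

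On contact with therapists:
- **RTG arm** (Intervention group): "participants allocated to the RTG training will receive 14 visits, each lasting 1 hour, from a research therapist over a period of 6 weeks", scheduled "three times a week for the first 3 weeks, twice a week for each of the next 2 weeks, then once in the final week". These visits are not simply added to usual care: "This will replace any usual care training for the upper limb".
- **Control arm** (Control group): usual care from NHS therapists, at variable intensity. One example is "These teams typically provide a service for 6 weeks, and patients may receive approximately two visits per week from a qualified therapist"; another is "Other patients may be seen by a community therapist once a fortnight with no supplementary visits from support staff". Some patients may have no therapy.

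The Data analysis section says that treatment received will be summarised by group, "as will the incidence of expected AEs and serious AEs". It mentions no split by route and plans no formal testing.

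All serious AEs go to the sponsor. If the chief investigator "considers any of these to be related to the RTG intervention, these AEs will be reported immediately to the research ethics committee". The same section warns that accidents may happen with the ARAT and WMFT equipment taken into participants' homes.

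**The concern.** The assessment question is symmetric; the staff route may not be. A participant seen 14 times by an unmasked research therapist has more occasions to mention a sore shoulder or swollen hand than a control seen fortnightly or not at all. If the routes are merged into one count per arm, part of any excess in the RTG column could reflect who was there to hear about the event.

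The table of AEs by arm is a main feasibility output, and readers planning the definitive trial will compare its columns even without a test.

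Two related points concern scope. The planned summary (expected and serious AEs) is narrower than aim 8, so an unexpected, non-serious event reported by staff has no stated place in the results. And the rule for immediate ethics-committee reporting refers only to the RTG intervention, although assessment equipment, used in both arms, is named as a source of accidents.

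**Working it through.** **Contacts.** The visit schedule reproduces the stated total: 3×3 + 2×2 + 1×1 = 14. From the Control group examples, over the same six weeks:
- about twice weekly: 2×6 = 12 visits, net difference 14 − 12 = 2
- once a fortnight: 6/2 = 3 visits, net difference 14 − 3 = 11
- no therapy: net difference 14

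**Possible size.** The article gives no AE rate, so this is an illustration. Assume the same true incidence *p* in both arms, and let:
- *a* = share of AEs captured by the assessment question
- *q* = chance that one therapist contact captures an AE the question would miss
- *k* = number of control contacts, half of them on average falling after the AE
- *w* = share of AEs falling in the six-week treatment window

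Spurious excess = *p*(1 − *a*)[(1 − *q*)^(*k*/2) − (1 − *q*)^7] × *w*

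Here *p*, *a*, *q* and *w* are all assumptions. With *w* = 6/26, AEs are spread evenly over six months; with *w* = 1, all fall in the treatment window. Results in percentage points for *p* = 0.5, against controls with 12 / 3 / 0 contacts:

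| *a* | *q* | *w* = 6/26 | *w* = 1 |
|---|---|---|---|
| 1.0 | 0.1 or 0.3 | 0 / 0 / 0 | 0 / 0 / 0 |
| 0.9 | 0.1 | 0.1 / 0.4 / 0.6 | 0.3 / 1.9 / 2.6 |
| 0.9 | 0.3 | 0.0 / 0.6 / 1.1 | 0.2 / 2.5 / 4.6 |
| 0.7 | 0.1 | 0.2 / 1.3 / 1.8 | 0.8 / 5.6 / 7.8 |
| 0.7 | 0.3 | 0.1 / 1.7 / 3.2 | 0.5 / 7.5 / 13.8 |
| 0.5 | 0.1 | 0.3 / 2.2 / 3.0 | 1.3 / 9.4 / 13.0 |
| 0.5 | 0.3 | 0.2 / 2.9 / 5.3 | 0.9 / 12.6 / 22.9 |

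Worked cell (*a* = 0.7, *q* = 0.3, no control therapy): 0.5 × 0.3 × (1 − 0.7^7) = 0.15 × 0.918 = 13.8 points; × 6/26 = 3.2 points. The excess is proportional to *p*, so at *p* = 0.3 every entry is 0.6 times as large. The model gives NHS therapists the same *q* as the research therapist. If they report less readily, the result moves towards the third figure in each cell.

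**Scale.** With 25 per arm, the 95% confidence half-width for a difference in incidence is 1.96 × √(2*p*(1 − *p*)/25): 25.4 points at *p* = 0.3 and 27.7 at *p* = 0.5. An excess of 3.2 points is 0.032 × 25 = 0.8 of a participant.

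**After the fix.** If the by-arm comparison uses only AEs elicited at assessments, the staff-contact term drops out and the excess in this model is zero by construction.

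**Scope, side by side.** Aim 8: AEs, unrestricted. Assessment question: expected AEs. Planned summary: expected and serious AEs. Unexpected non-serious AEs can arrive only through staff or volunteered reports, and are not in the stated summary.

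**The case against.** The strongest reply is that core ascertainment is already balanced. Every expected AE is asked about directly, on one schedule, at visits conducted by a blinded assessor. If that question works well there is nothing left for the extra contacts to find. This stands, and it is why the artefact may be zero. It does not settle the matter: intervals between assessments run to about three months, people with aphasia may take part, and complete recall is not assured.

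Second, staff training is universal as worded, and Trial monitoring and management provides for training site clinical staff. So the documents do not show that therapists treating controls are untrained. That also stands. However, that training takes place before the study starts, the Discussion reports about 100 clinical personnel with high turnover, and the treatment details listed for the usual-care recording sheets do not include AEs.

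Third, counting rules belong in the SAP or full protocol, which are not shown. This disposes of any complaint that the article lacks a rule for symptoms already present at baseline. Such symptoms are in any case not a source of bias between randomized arms. It does not dispose of the scope point, because the article itself states a summary narrower than aim 8.

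A reader might go further and infer that RTG participants have 14 extra contacts, or 17 research contacts (14 + 3 assessments) against 3. The documents do not support this as the measure of imbalance: the visits replace usual arm therapy, and the staff route is not confined to research staff. A reader might also take an illustration such as 40% true incidence with 90% against 50% detection, giving 36% against 20%, as the likely effect. Those detection rates are assumptions applied to the whole follow-up. With events spread evenly and the therapist's contribution confined to the treatment window, the 16-point gap becomes 16 × 6/26 = 3.7 points.

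**Conclusion.** The point holds as a caution about differential ascertainment, with a cheap remedy. RTG participants have about 2 to 14 more therapist contacts during the intervention, and merging the routes may inflate their AE frequency.

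The size cannot be derived from the document. Under the stated assumptions, with true incidence of 30% to 50%, it is zero if the assessment question captures everything. It is about 0 to 3 points over six months if the question captures 70% to 90%, and about 0 to 14 points if all AEs fall in the treatment window. With only 50% capture the upper values are about 5 and 23 points. The descriptive confidence half-width is about 25 to 28 points.

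It would be wrong to conclude that the table will show an excess due to surveillance alone. The Adverse events section names a real mechanism by which greater arm use could lead to more falls, so an observed excess could be genuine, artefactual or both. The present summary would not help a reader tell which.

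The mismatch between the planned summary and aim 8 is plain from the text. On ethics-committee reporting, the rule and the statement about assessment equipment sit in the same section and need reconciling. It should not be inferred that assessment-related serious AEs go unreported, since all serious AEs go to the sponsor.

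**What to change.** 1. Record the source of each AE: elicited at a scheduled assessment, or reported by treating staff or otherwise.
2. Make AEs elicited at the scheduled assessments the main by-arm summary.
3. List AEs reported by treating staff separately by arm, with the number of therapist contacts in each arm. The RTG therapist's log and the usual-care recording sheets should supply those counts.
4. Summarise all recorded AEs, including unexpected non-serious ones, so that the analysis matches aim 8.
5. Reconcile the ethics-committee reporting rule with the statement that accidents may happen with assessment equipment used in both arms.

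The cost is a little more data tagging and a change of analysis wording; the main by-arm count will be lower than the total count. Items 1 to 4 need no new question to participants, which matters because Trial status reports 46 of the planned 50 already enrolled. Tagging past events assumes that existing records show who reported each one. The change reduces the bias without removing it entirely: participants are unmasked, and frequent contact may still affect what they recall at assessment.

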### Data analysis

As this is a feasibility study to test the levels of recruitment and retention of participants, and completeness of data that can be expected within a definitive multicenter trial, there will be no formal statistical testing, and results will instead be summarized using descriptive statistics.

Analysis of the centrally held screening log data will lead to a description of the characteristics of the recruited sample against the target population, and the percentage of refusals at the recruitment stage. Recruitment rates per month for each site will be determined. The number of withdrawals and reasons for withdrawal from the study will be assessed.

Compliance with the RTG intervention will be assessed by the number and duration of physiotherapy visits and the proportion of participants completing the 6-week intervention. The frequency of use of the exercises, number of repetitions, and duration of practice of each exercise, both within the physiotherapy sessions, and the independent practice will be summarized and compared with the intended exercise frequency and content. The frequency and content of the treatment received by each group will be summarized, as will the incidence of expected AEs and serious AEs. Responses to the participant questionnaire about the RTG training will be synthesized and examined to determine if any changes should be made to the intervention.

Completeness of outcome data will be determined, and data for each of the endpoints will be summarized; the mean differences between the arms, with their confidence intervals, will be presented. Assessment of the sample scores on the outcome measures, combined with a summary of participant preference for ARAT and WMFT, will be carried out to determine which arm function test should be used as the primary outcome measure for a phase III trial. Sample sizes for a subsequent phase III trial will be calculated, based on observed changes from baseline in performance, for both the control and intervention groups.

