**Methods/design:**

This is to be a randomized controlled feasibility trial recruiting 50 individuals with upper-limb motor impairment after stroke. Participants will be recruited after discharge from hospital and up to 12 months post-stroke from hospital stroke services and community therapy-provider services. Participants will be assessed at baseline, and then electronically randomized and allocated to group by minimization, based on the time post-stroke and extent of upper-limb impairment. The intervention group will receive 14 training sessions, each 1 hour long, with a physiotherapist over 6 weeks and will be encouraged to practice independently for 1 hour/day to give a total of 56 hours of training time per participant. Participants allocated to the control group will receive arm therapy in accordance with usual care. Participants will be measured at 7 weeks post-randomization, and followed-up at 3 and 6 months post-randomization. Primary outcome measures for assessment of arm function are the Action Research Arm Test (ARAT) and Wolf Motor Function Test (WMFT). Secondary measures are the Motor Activity Log, Stroke Impact Scale, Carer Strain Index, and health and social care resource use. All assessments will be conducted by a trained assessor blinded to treatment allocation. Recruitment, adherence, withdrawals, adverse events (AEs), and completeness of data will be recorded and reported.

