### Study objectives

The aims of this feasibility trial are as follows.

1. To determine the characteristics of the sample entering the feasibility trial for its representation of the target population and to determine the most appropriate primary outcome measure for the sample, that is, the Action Research Arm Test (ARAT) or the Wolf Motor Function Test (WMFT).

2. To estimate identification and recruitment rates for the trial across multiple sites.

3. To determine the frequency and content of upper-limb treatment delivered to both the intervention and control groups.

4. To estimate the adherence of RTG group participants to the prescribed schedule.

5. To estimate the completeness of outcome data.

6. To calculate sample sizes for a subsequent definitive trial, based on measured changes in performance for both the control and intervention groups.

7. To collect and synthesize the views from participants in the intervention group to determine acceptability of the RTG therapy.

8. To determine the frequency of AEs in both groups.

9. To collect data on health and social care resource use to inform data-collection methods for an economic evaluation in the subsequent definitive trial.

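### The planned AE summary covers only expected and serious AEs, which is narrower than aim 8 and leaves recorded unexpected non-serious AEs without a place in the results

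*Protocol article*

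**What the plan says.** Three places in the protocol article speak of AEs without restriction.

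- Study objectives, aim 8: "To determine the frequency of AEs in both groups".
- Abstract, Methods/design: "Recruitment, adherence, withdrawals, adverse events (AEs), and completeness of data will be recorded and reported".
- Adverse events, on staff: "All staff involved in contact with participants will receive training on identification and reporting of AEs". The same section has the trial manager collect AE incidence and pass it to the steering group each quarter.

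Two places are restricted.

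- Adverse events, on what participants are asked: "Participants will be specifically asked at each of the assessment visits if they have experienced any of the expected AEs". The expected events are a short list. The first part reads "Pain in the shoulder, upper arm and hand and oedema in the hand are common sequelae of hemiparesis, and are therefore expected AEs"; the second reads "falls and equipment failure leading to injury requiring a visit to hospital or general practitioner will be treated as expected AEs".
- Data analysis, on what is summarised: "as will the incidence of expected AEs and serious AEs".

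**The concern.** The statement of what will be analysed is narrower than the aim it serves. An AE that is neither on the expected list nor serious belongs to aim 8, and staff are trained to report it, yet an analyst who followed the Data analysis section as worded would not tabulate it.

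The class is not an empty one for this intervention. The pain and oedema items are on the list because they commonly follow hemiparesis. The training itself prescribes 56 hours of practice, aims for 100 to 300 repetitions in each supervised hour, and names elbow extension among the movements for part-practice (Background; Intervention group). Non-serious elbow, wrist or neck pain from such practice is plausible and is not on the list.

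At stake is one of the outputs the study exists to supply. The Background names the incidence of AEs among the things to be determined before a definitive trial is designed. The trial also runs without an independent data monitoring and safety committee, partly on the ground that intervention-related AEs are very unlikely (Trial monitoring and management). A full AE summary would let readers check that premise.

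**Working it through.** No arithmetic applies: the study plans no formal testing, and the point concerns scope. The check is to follow each class of AE through the steps that the article states.

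| AE class | Within aim 8 and the abstract | Participants stated to be asked | Staff can report, trial manager collects | Named in the planned summary |
|---|---|---|---|---|
| Expected | yes | yes | yes | yes |
| Serious | yes | only if also on the expected list | yes, and reported to the sponsor | yes |
| Unexpected, non-serious | yes | no | yes | no |

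**Step 1: scope of the aim.** Aim 8 and the abstract cover all three rows.

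**Step 2: collection.** The prompted question reaches the first row, and serious events only where they are on the list. The staff route reaches all three rows, because neither the training sentence nor the trial manager's collection is confined to expected or serious events. The third row is therefore recordable.

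**Step 3: summary.** The Data analysis section names the first two rows only. The third row is where recording and stated reporting part company.

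**Step 4: is the staff route even between arms?** It depends on how often trained staff see the participant.

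- Intervention group: 14 one-hour visits from a research therapist over 6 weeks, that is 3 × 3 + 2 × 2 + 1 = 14. Participants also record reasons for not keeping to the practice schedule and answer a questionnaire about the training.
- Control group: usual care, which ranges from about two visits a week, through one a fortnight, to no therapy at all (Control group section).
- Both groups: the same assessment visits, but the only AE enquiry stated for them concerns the expected events.

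So a count of unexpected non-serious AEs would carry a difference in opportunity to report as well as any difference in occurrence. It would probably favour detection in the intervention group. A table for this class is still needed, with that caveat beside it.

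**The case against.** The strongest objection is that the article does not let such events vanish. Contact staff are trained to report AEs of any kind, the trial manager collects them, and the steering group discusses them. Unlisted problems could also surface through reasons for withdrawal, reasons for non-adherence and the participant questionnaire, all of which are stated outputs. This stands. A reader might infer that any unforeseen non-serious harm drops out, or that the study can detect only the harms it already expects. The documents do not support either reading. Nor would the class be reported as zero: a summary with no row for a class makes no statement about it.

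A second objection is that an article condenses. The wording of the AE form and the layout of AE tables usually sit in the full protocol, the case report form or the SAP, none of which is shown, and being specifically asked about some events does not mean that nothing else is asked. This stands for the open question, whose absence from the article is not in itself an error. It does not dispose of the summary, because there the article does not merely omit detail: it states which AEs will be summarised, and the statement is narrower than its own aim.

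A third objection is that the list is not wholly detached from the training. Falls are linked to greater activity following increased arm use, and pain in the shoulder, upper arm and hand covers much of the trained limb. Also true. It makes the unlisted class smaller without bringing it into the summary.

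**Conclusion.** The point holds as a mismatch of scope. The Data analysis section commits to summarising two classes of AE where aim 8 and the abstract call for all of them, so unexpected non-serious AEs can be recorded but have no stated place in the results. A secondary weakness follows: on the article's account, capture of this class relies on unprompted reports, and the contact that generates them differs by arm.

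The size is one AE class of three. The number of events affected cannot be derived, because the article gives no incidence for them; any assumed incidence would show only that events might occur, not that they would be lost. The conclusion rests on reading the summary sentence as complete for AEs, and on the full protocol, case report form and SAP not already widening it. The point is a modest one, worth correcting because the correction is nearly free.

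**What to change.** **Main change.** In the Data analysis section, replace the reference to expected and serious AEs with: *all recorded AEs (expected, unexpected non-serious, and serious), by arm*. Add one sentence noting that events outside the prompted list were ascertained from unprompted reports under unequal staff contact between arms, so their counts should not be read as a like-for-like comparison. The cost is one more group of rows in the AE table and no new data collection, and the change remains possible with 46 of the planned 50 participants enrolled.

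**Secondary and optional.** If the full protocol or case report form does not already have one, add a single open AE question, identical in both arms, at the remaining assessment visits. Its costs are larger. A change to trial documents needs the sponsor's approval and then submission to the ethics committee and the R&D departments (Ethical considerations). With 46 of 50 already enrolled, the question would reach only the visits still to come, so ascertainment would be mixed across participants and the report would have to say so. Some unrelated minor complaints would be recorded. If the blinded assessor asks it, the wording should steer participants away from describing their treatment, in keeping with the Blinding section.
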